# Study Protocol

**Title:** Effect of early mobilization combined with early nutrition on acquired weakness in ICU patients

**Director:** [name]

**Purpose:** This study adopted Orem self-care theory as the framework of early mobilization (EM) intervention, and European Society for Parenteral and Enteral Nutrition (ESPEN) guideline (2019) of early nutrition intervention, aiming to construct an innovative intervention strategy against intensive care unit-acquired weakness (ICU-AW), and to investigate whether the participation in early mobilization combined with early nutrition (EMN) program in the ICU is better than EM alone or routine ICU care.

**Study content: (describe only the necessary part related to the implementation of the study)**

## 1. Participants

### 1.1 Sampling and group allocation

#### 1.1.1 Sampling

Convenient sampling method will be adopted. Through case books or face-to-face inquiry, patients admitted to ICUs of the Second Affiliated Hospital of Harbin Medical University and the First Affiliated Hospital of Jiamusi University will be screened, and the patients or their agents will be informed of the purpose and significance of this study by telephone or face-to-face. On the premise of informed consent, the patients who meet the inclusion criteria will be included in this study.

### 1.1.2 Group allocation

Simple random grouping with Excel will be applied in this trial.

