### 1.2 Sample size calculation

With a power of 90% and 2-sided 5% level of significance, 49 participants per group (147 total) will be needed to detect a significant between-group difference in the primary outcome, as calculated by PASS (version 11.0.7) and allowing for up to 10% attrition at ICU discharge (i.e., 132 participants with complete data). The estimated effect size is based on the incidence of ICU-AW at ICU discharge (early mobilization group=33.1%, control group=51.9%) reported in a meta-analysis of early mobilization interventions for critically ill patients [1] as well as the findings of Chen (2017) in a clinical trial (15.9%) [2].

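### Simple randomization leaves hospital balance to chance, and possibly the arm sizes too; 1:1:1 permuted blocks stratified by hospital are a cheap improvement

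*Protocol*

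**What the plan says.** Protocol section 1.1.2 (Group allocation) consists of one sentence: "Simple random grouping with Excel will be applied in this trial". It gives no ratio, blocking or stratification, and does not say how Excel is to be used.

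Section 1.1.1 (Sampling) makes this a two-hospital trial with convenience recruitment: "patients admitted to ICUs of the Second Affiliated Hospital of Harbin Medical University and the First Affiliated Hospital of Jiamusi University will be screened". The expected number from each hospital is not stated.

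Section 1.2 (Sample size calculation) plans equal groups: "49 participants per group (147 total) will be needed to detect a significant between-group difference in the primary outcome". The setting is "With a power of 90% and 2-sided 5% level of significance", with a 10% allowance for attrition that leaves 132 complete participants.

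Section 2.2.1 describes usual care as dependent on the clinician. Rehabilitation is ordered for some patients only, with content left to the therapist, and doctors differ in when and by what route they start nutrition. Section 4 gives chi-squared tests for categorical data and does not mention hospital.

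**The concern.** Simple randomization in its usual sense draws each patient independently. It fixes neither the arm totals nor each hospital's share of each arm. Two things could follow.

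- **Arm sizes.** The sample size assumes equal groups. Unequal groups can lower the power of a test planned at just over 90%.
- **Hospital.** The two treatment components under test, mobilization and nutrition, are the same parts of usual care that section 2.2.1 leaves to individual clinicians. Clinicians work within hospitals, so the background level of both may differ by site. If one arm happens to hold more patients from one hospital, the arm comparison is partly a hospital comparison in that realised trial. With about 49 patients per arm, such imbalances are not rare.

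Both can be prevented before enrolment at almost no cost. Afterwards, hospital imbalance can only be adjusted for.

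**Working it through.** **Inputs.** From section 1.2: 147 patients, three groups, 132 completers (44 per group), two-sided alpha 0.05, weakness rates of 51.9% (control) and 33.1% (early mobilization), and a further rate of 15.9% from a cited clinical trial. *Assumption:* 15.9% is the combined arm. *Assumption:* hospital splits of 50:50, 70:30, 80:20 and 90:10, because none is given.

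**Step 1. Reproduce the stated size.** For a three-group chi-squared test (2 df, critical value 5.991), the noncentrality is λ = Σ nᵢ(pᵢ − p̄)² / [p̄(1 − p̄)].

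- p̄ = (0.519 + 0.331 + 0.159)/3 = 0.3363
- Σ(pᵢ − p̄)² = 0.03337 + 0.00003 + 0.03145 = 0.06484
- With 44 per arm: λ = 44 × 0.06484 / (0.3363 × 0.6637) = 12.78, so power is 90.3%. With 43 per arm it is 89.6%.
- 44/0.9 = 48.9, rounded up to 49 per arm, or 147 in total.

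The plan's figure reproduces under this reading.

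**Step 2. Arm sizes under independent draws.** Arm sizes are multinomial(147; 1/3, 1/3, 1/3). The SD of one arm is √(147 × 1/3 × 2/3) = 5.7. Exact enumeration gives:

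| Event | Probability |
|---|---|
| Exactly 49/49/49 | 0.56% |
| Largest minus smallest ≥ 10 | 60% |
| Largest minus smallest ≥ 15 | 31% |
| Largest minus smallest ≥ 20 | 12% |

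**Step 3. Effect on power.** I computed λ for every possible split, scaled to completers by 132/147, and weighted by its probability.

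- Average power is 90.0%, against 90.3% with equal arms: a loss of about 0.3 points.
- Power is below 88% in about 14% of trials.
- For arms of 40, 49 and 58, power depends on which arm is which. It is 86.6% with control 49, mobilization 58 and combined 40, and 92.9% with control 49, mobilization 40 and combined 58.

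**Step 4. Hospital share.** Each hospital's patients were drawn independently into three arms by simulation. The spread is the highest minus the lowest arm in the share from one hospital.

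| Assumed split | Median spread (points) | P(spread ≥ 15) | P(spread ≥ 20) |
|---|---|---|---|
| 50:50 | 11.5 | about 30% | 12% |
| 70:30 | 10.5 | about 24% | 8% |
| 80:20 | 9.1 | about 15% | 4% |
| 90:10 | 7.0 | about 4% | 0.2% |

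These are worst-pair figures over three arms. For one given pair at 50:50, the chance of a difference of 15 points or more is about 14%.

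**Step 5. The other reading of Excel grouping.** If random numbers are sorted over one fixed list of 147 and cut into three sets of 49, arm sizes are exactly equal once the list is filled, and Steps 2 and 3 fall away. Hospital share is still not controlled. Repeating Step 4 with arms fixed at 49 (hypergeometric draws) gives a spread of 15 points or more in about 28%, 22%, 14% and 3% of trials for the four splits, little different from the table.

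**The case against.** The strongest reply is that simple randomization is valid: expected imbalance is zero, tests keep their level, and 49 per group is a planning figure that need not be met exactly. This stands. That 49/49/49 arises in only 0.56% of trials is no measure of harm, and Step 3 shows that the average power loss is negligible.

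Three stronger readings are tempting, and the documents do not support them.

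- *The size calculation is undermined.* It is not. It reproduces, and unequal arms cost about 0.3 points on average.
- *The hospitals will be unbalanced.* Imbalance is a chance event whose probability depends on a split that the protocol does not give. Nor does section 2.2.1 describe any difference between the two hospitals; it describes differences between doctors and therapists. That hospital is prognostic is a plausible inference, and stratifying by hospital would not remove variation between doctors within a hospital.
- *Recruiters can see the next allocation in an open spreadsheet.* Section 1.1.2 names a tool. It does not say who makes or holds the list, or who can see it.

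Adjustment for hospital may also sit in a statistical analysis plan that is not shown, so its absence from section 4 is not counted here.

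Finally, independent draws are the least predictable method, and small blocks at each hospital add some predictability where treatment is visible to staff. That is a real cost, but varying and concealing the block sizes limits it.

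What remains is that under either reading of the allocation sentence, nothing stated controls hospital balance, and a better method is available for almost nothing.

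**Conclusion.** The point holds as a cheap design improvement, minor to moderate in weight. It is not an error that invalidates the trial. Under independent draws, a gap of 10 or more between arms is more likely than not, with little effect on average power. The stronger reason to change is hospital: a spread of 15 points or more would arise in up to about three trials in ten if the hospitals contribute equally, falling to about one in 25 at 90:10.

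The conclusion rests on three assumptions: 15.9% is the combined-arm rate, the hospital split lies between 50:50 and 90:10, and hospital is related to outcome. The size of that last relation is not given, so the resulting distortion of the treatment comparison cannot be quantified from the protocol.

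**What to change.** Replace the sentence in section 1.1.2 with a short paragraph stating:

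- 1:1:1 allocation in randomly permuted blocks of varying size (for example 3, 6 and 9), stratified by hospital, with block sizes not disclosed to recruiting staff;
- a list generated and held by someone who does not recruit, with each allocation released only after the patient is enrolled and enrolment data are recorded (sequentially numbered opaque sealed envelopes would suffice);
- hospital, as the stratification factor, accounted for in the primary analysis, for example by a Cochran–Mantel–Haenszel test stratified by hospital or a logistic model with hospital as a covariate.

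With these blocks, an unfinished block of 9 can leave two arms at most 3 apart within a hospital, so at most 2 × 3 = 6 apart overall. Arm sizes and hospital shares are then both held close to plan.

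The cost is a one-paragraph amendment and about an hour of list preparation. The downside is slight predictability at the ends of blocks. The change to allocation helps only patients not yet randomized. If enrolment is complete, state how Excel was used, report hospital by arm, and adjust for hospital.

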### 1.2 Sample size calculation

With a power of 90% and 2-sided 5% level of significance, 49 participants per group (147 total) will be needed to detect a significant between-group difference in the primary outcome, as calculated by PASS (version 11.0.7) and allowing for up to 10% attrition at ICU discharge (i.e., 132 participants with complete data). The estimated effect size is based on the incidence of ICU-AW at ICU discharge (early mobilization group=33.1%, control group=51.9%) reported in a meta-analysis of early mobilization interventions for critically ill patients [1] as well as the findings of Chen (2017) in a clinical trial (15.9%) [2].

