### 4. Statistical analysis

Statistical analyses will be conducted by an independent statistician using SPSS Statistics software (version 20.0) adopting two-tailed tests, with *p* values below 5%

indicating statistical significance.

Continuous data were expressed as mean  $\pm$  standard deviation (normal variables) or medians (non-normal variables), and categorical data were presented as number (%). Normal variables among three groups were compared by one-way ANOVA analysis, non-normal variables and ranked data with nonparametric Kruskal Wallis test, and categorical data (except for ranked data) as well as their pairwise comparisons with Chi-squared test. The data of three groups at different time points will be compared by repeated measurement analysis of variance.

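### The 90% power in section 1.2 fits only the three-group test; EMN versus EM, one of the two comparisons in the Purpose, has about 48%

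*Protocol*

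**What the plan says.** Protocol section 1.2 gives one power figure: "With a power of 90% and 2-sided 5% level of significance, 49 participants per group (147 total) will be needed to detect a significant" difference among the groups in the primary outcome. The loss allowance is "allowing for up to 10% attrition at ICU discharge (i.e., 132 participants with complete data", which is 44 per group.

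The planning rates are the "incidence of ICU-AW at ICU discharge (early mobilization group=33.1%, control group=51.9" (both percentages), taken from a meta-analysis. A third rate, 15.9%, comes from a single clinical trial and is not assigned to a group. The section does not say which test, or which pair of groups, the 90% belongs to.

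The Purpose sets the question as whether the combined "program in the ICU is better than EM alone or routine ICU care". Section 4 analyses "categorical data (except for ranked data) as well as their pairwise comparisons with Chi-squared test", with significance at p below 5%.

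**The concern.** A test across three groups shows only that the rates differ somewhere. The Purpose asks about two particular pairs, and the pairwise tests of section 4 are what address them. A reader who sees a single 90% will naturally carry it over to those pairs.

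The EM group is in the design so that the effect of nutrition can be separated from that of mobilization. EMN against control mixes the two; only EMN against EM isolates nutrition. If that contrast has far less than 90% power, a non-significant result is close to an even chance even when nutrition does all that was assumed. Under a 90% label, that result could be read as showing that nutrition adds nothing.

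**Working it through.** **Inputs.** All are from section 1.2: two-sided 5%; rates of 0.519 (control), 0.331 (EM) and 0.159; 44 completers or 49 enrolled per group. Taking 0.159 as the EMN rate is an inference, tested in step 1.

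**1. Reproducing the stated size.** For a 3×2 chi-squared test with n per group, the non-centrality is λ = n · Σ(pᵢ − p̄)² / [p̄(1 − p̄)].

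- p̄ = (0.519 + 0.331 + 0.159)/3 = 0.3363, so p̄(1 − p̄) = 0.2232.
- The squared deviations are 0.03337 (control), 0.00003 (EM) and 0.03145 (EMN), with sum 0.06484.
- λ = n × 0.06484/0.2232 = 0.2905n.
- The critical value on 2 df is 5.991. At n = 43, λ = 12.49 and power is 89.6%. At n = 44, λ = 12.78 and power is 90.3%.
- 44 × 3 = 132; 44/0.9 = 48.9, so 49; 49 × 3 = 147.

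All the stated numbers match. EM lies almost at the mean rate and contributes practically nothing to λ, so the global test is driven by control against EMN.

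**2. Could a pairwise test give the same size?** For 90% power at two-sided 5%, n = [1.960·√(2p̄(1 − p̄)) + 1.282·√(p₁q₁ + p₂q₂)]² / (p₁ − p₂)², where p̄ is now the mean of the pair and q = 1 − p.

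| Contrast | Completers per group | Enrolled per group at 10% loss |
|---|---|---|
| EMN v control | 35 | 39 |
| EMN v EM | 130 | 145 |
| EM v control | 144 | 160 |

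None gives 44. A continuity correction (40, 141, 154) or a one-sided test (28, 106, 117) does not give it either.

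**3. Power of the pairwise tests at 44 per group.** By normal approximation, z = [d√n − 1.960·√(2p̄(1 − p̄))] / √(p₁q₁ + p₂q₂), where d is the difference in rates:

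- EMN v EM: d = 0.172; (1.141 − 1.192)/0.596 = −0.086, power 46.6%.
- EM v control: d = 0.188; (1.247 − 1.370)/0.686 = −0.179, power 42.9%.
- EMN v control: d = 0.360; (2.388 − 1.312)/0.619 = 1.738, power 95.9%.

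Summing exact binomial probabilities for the uncorrected chi-squared test gives:

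| Contrast | 44 per group | 49 per group (no attrition) |
|---|---|---|
| EMN v control | 96.3% | 97.4% |
| EMN v EM | 48.3% | 51.5% |
| EM v control | 43.0% | 47.9% |

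**4. What EMN v EM can detect.** With 44 per group and EM at 33.1%, exact power is 90.4% if the EMN rate is 7% and 93.3% if it is 6%. An EMN rate of about 7%, less than half of 15.9%, would be needed for 90%.

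**5. Expected precision.** At the planning rates the standard error of the EMN v EM risk difference is √[(0.331 × 0.669 + 0.159 × 0.841)/44] = 0.0898. The 95% interval is therefore about ±17.6 percentage points around an expected difference of 17.2.

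**The case against.** The strongest reply is that section 1.2 contains no wrong figure. It claims 90% for a difference between groups in a three-group trial, the global test delivers it, and section 4 allows for a global chi-squared test before the pairwise ones. That stands: a reader might infer an arithmetic error, and there is none. The defect is that one unlabelled figure is given beside pairwise questions to which it does not all apply.

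The Purpose names two comparators and ranks neither. EMN against routine care is well powered, and read literally as one or the other, the chance of at least one significant result is about 97% by simulation at unadjusted 5%. So it would be too strong to call EMN against EM the comparison the trial exists for, or to call the trial underpowered as a whole. EM against control is not in the Purpose, so its low power does not undercut a stated aim.

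The EMN label on 15.9% and the 2-df test are inferred. This too stands, but 44, 49, 132 and 147 all following from them makes the inference strong.

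The allowance is for up to 10% loss. With no loss, EMN against EM reaches about 51%, so power below one half is not unconditional. The gap to 90% hardly changes.

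An analysis plan that is not shown might settle how contrasts are reported. It could not raise the power of 44 per group, and the 90% is stated in the protocol itself.

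**Conclusion.** The point holds as one of attribution and disclosure. The single 90% belongs to the global three-group test and does not carry over to EMN against EM, one of the two comparisons in the Purpose and the only one that isolates the added effect of nutrition. Power there is about 48% with the full 10% attrition and about 51% with none. EMN against control has about 96%. EM against control has 43% to 48%, but is not a stated aim.

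These figures rest on the protocol's three rates, on 15.9% being the EMN rate, and on an unadjusted two-sided 5% for each pair. The protocol states no multiplicity adjustment. If 0.05/3 were used, power at 44 per group would be about 90% (EMN v control), 30% (EMN v EM) and 27% (EM v control).

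**What to change.** Reword section 1.2 to say that 90% is the power of the global 2-df chi-squared test at control 51.9%, EM 33.1% and EMN 15.9%, labelling the last rate if that is the intended assignment. Give the pairwise powers at 44 completers per group beside it: about 96% for EMN v control, 48% for EMN v EM and 43% for EM v control.

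Add to section 4 that EMN v EM will be reported as a risk difference with a 95% confidence interval, and that a non-significant result there is not evidence that nutrition adds nothing.

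How the contrasts are ranked is for the sponsor. Making EMN v control primary only because the sample size suits it would fit the objective to the sample and would still not isolate nutrition.

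The cost is a wording change in two sections and a less favourable stated power for two contrasts. No extra patients are needed.

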### 3. Outcomes

Table 1. Outcome assessment.

| Outcomes                           | Timepoint                                                     |
|------------------------------------|---------------------------------------------------------------|
| Baseline characteristics           | Enrolment                                                     |
| BI                                 | Enrolment, every 24 hours following enrollment, ICU discharge |
| MRC sum-score                      | Enrolment, ICU discharge                                      |
| SOFA score                         | Enrolment, every 24 hours following enrollment, ICU discharge |
| Time of ICU stay                   | ICU discharge                                                 |
| Duration of mechanical ventilation | ICU discharge                                                 |
| ICU mortality                      | ICU discharge                                                 |

BI = Barthel index, ICU = intensive care unit, ICU-AW = intensive care unit-acquired weakness, MRC = Medical Research Council, SOFA = Sequential Organ Failure Assessment.

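### The protocol does not say how ICU deaths enter ICU-AW, ICU stay and ventilation time; by default they drop out of the primary and count as short durations, which distorts the comparison if deaths differ between arms

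*Protocol*

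**What the plan says.** Protocol section 1.2 states "49 participants per group (147 total) will be needed to detect a significant between-group difference in the primary outcome", based on the "incidence of ICU-AW at ICU discharge (early mobilization group=33.1%, control group=51.9"%) and on a third rate of 15.9% from a clinical trial. It allows for missing outcomes in one phrase: "allowing for up to 10% attrition at ICU discharge (i.e., 132 participants with complete data". Death is not mentioned there.

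Section 3, Table 1, schedules the MRC sum-score, its only muscle-strength measure, at enrolment and at ICU discharge. The same table lists "ICU mortality", ICU stay and "Duration of mechanical ventilation" as outcomes, all taken at ICU discharge.

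Section 4 assigns tests by type of variable: one-way ANOVA for normal variables, "non-normal variables and ranked data with nonparametric Kruskal Wallis test", and chi-squared tests for categorical data. It does not say who is included or how patients who die are coded.

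Section 1.3.2, item 7, excludes patients with terminal cancer and those in whom death or a very poor outcome is anticipated.

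**The concern.** A discharge strength score exists only for patients who leave the ICU alive. The primary comparison therefore runs in a subset formed after randomisation, and what forms it is survival, which the trial itself lists as an outcome that the arms may change. If survival differs between arms, or if different kinds of patient die, the survivors are no longer comparable by randomisation.

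The durations have the opposite problem. Patients who die do have a recorded ICU stay and ventilation time, and an early death gives a short one. Placed in ANOVA or Kruskal-Wallis as recorded, it counts as a good result. At stake is whether a lower ICU-AW rate or a shorter stay reflects the intervention or reflects deaths. If the rule stays open, it can be chosen after the results are known.

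**Working it through.** **1. The plan's own figure.** Inputs from section 1.2: rates 0.519, 0.331 and 0.159, "2-sided 5% level of significance", power 90%, three equal groups. That 15.9% is the combined-group rate is an assumption, supported by the fact that the stated sample size then reproduces.

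Mean rate = (0.519 + 0.331 + 0.159)/3 = 0.336. Effect size w² = [mean squared deviation]/[0.336 × 0.664] = 0.0968, so w = 0.311. For the overall chi-squared test on 2 degrees of freedom, 131 patients give 90% power, hence 44 per group (132), with power 0.903. Then 44/0.9 = 48.9, so 49 per group and 147 in total. The stated size is correct for this test.

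**2. Power if deaths come on top of other losses.** The documents give no mortality rate, so these are assumed values.

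| Deaths + other loss | Evaluable | Power |
|---|---|---|
| 10% in total | 132.3 | 0.904 |
| 5% + 10% | 124.9 | 0.886 |
| 10% + 10% | 117.6 | 0.865 |
| 20% + 10% | 102.9 | 0.814 |

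**3. Survivor-only ICU-AW with no true effect.** Let every arm have an underlying weakness risk of 0.519, mortality m, and a share s of deaths among weak patients. Observed ICU-AW in survivors = (0.519 − m·s)/(1 − m).

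| s | m = 10% | m = 20% | Apparent gain for the 20% arm |
|---|---|---|---|
| 0.519 (death unrelated to weakness) | 51.9% | 51.9% | 0 |
| 0.8 | 48.8% | 44.9% | 3.9 points |
| 1.0 | 46.6% | 39.9% | 6.7 points |

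A second model, with deaths confined to a frail 35% of patients (weakness risk 0.85 against 0.34 in the rest), gives (0.15 × 0.85 + 0.65 × 0.34)/0.80 = 43.6% and (0.25 × 0.85 + 0.65 × 0.34)/0.90 = 48.2%, a gap of 4.6 points. With equal mortality and the same mix of deaths the gap is 0. If the control arm has the higher mortality, the sign reverses.

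**4. ICU stay with no effect in survivors.** Assume a mean of 10 days in survivors and 4 days to death. Then 10% mortality gives 0.9 × 10 + 0.1 × 4 = 9.4 days, and 20% gives 0.8 × 10 + 0.2 × 4 = 8.8 days: an apparent gain of 0.6 days from deaths alone.

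Kruskal-Wallis was simulated with two arms of 49, lognormal times, survivor median 7 days and log-SD 0.5. Rejection rates at a nominal 5%, with 10% mortality in the other arm:

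| Mortality in the worse arm | Median time to death 3 days | 5 days | 7 days |
|---|---|---|---|
| 25% | 17% | 7% | 5% |
| 20% | 10% | 6% | 5% |
| 15% | 5–6% | 5–6% | 5–6% |

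**5. An analysis that counts death as failure.** With equal mortality m in all arms, each rate p becomes m + (1 − m)p. At m = 10% the rates are 56.7%, 39.8% and 24.3%. Power of the overall test is 0.842 with all 147 evaluable and 0.799 with 132. At m = 20% with all 147 it is 0.727. Keeping 90% power would need 58 evaluable per group at 10% mortality and 76 at 20%, against 44 planned.

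Under the no-effect model of step 3, ICU-AW or death is 51.9% in both arms when s = 1.0, and 53.9% (m = 10%) against 55.9% (m = 20%) when s = 0.8. The spurious gain for the higher-mortality arm disappears.

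**The case against.** The strongest reply is that the protocol states no rule at all. A reader might infer that it treats deaths as attrition and as short stays, but no section says so. A statistical analysis plan, not available here, could set the rule, and handling of deaths is often left to that document. This stands against any claim that the protocol prescribes a wrong rule. It does not remove the point. The protocol itself fixes the measurement schedule, the size of the evaluable set and the tests for the durations, and following these as written gives the default described above.

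A reader might also infer that deaths bias the comparison in any event. They do not: steps 3 and 4 show no distortion when mortality and the mix of deaths are equal, when death is unrelated to weakness, or when deaths occur as late as discharges. An intervention that saves lives would look worse on ICU-AW, not better.

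The sizes rest on assumed inputs. No mortality rate is given, and the exclusion in section 1.3.2 lowers the number of deaths to expect. The 17% rejection rate is the top of its range. All of this stands.

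ICU mortality is reported separately, so a large excess would be seen. That helps in part only: with 49 per arm, a difference such as 20% versus 10% would usually not reach significance, yet could still move the other comparisons.

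Finally, replacing the primary by a composite with death would change the question from weakness to weakness or death and would cost power. That objection stands, and the fix below leaves the primary as it is.

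**Conclusion.** The point holds as a gap with a predictable default, not as an error in a stated rule. ICU-AW can be observed only in patients alive at ICU discharge, and nothing in the duration analyses separates death from discharge. If mortality, or the weakness of those who die, differs between arms, both comparisons are distorted, and the direction can be either.

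The size cannot be derived from the documents. Under assumed mortality of 20% versus 10% and no true effect, survivor ICU-AW favours the higher-mortality arm by about 4 to 7 points when deaths fall mainly on weak patients, and by 0 when death is unrelated to weakness. For stay, false rejection runs from about 5% to 17% at 15–25% versus 10% mortality, depending on how early deaths occur. For scale, the planned control versus early mobilization difference is 51.9 − 33.1 = 18.8 points.

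The sample size itself reproduces, and this point gives no reason to change it. It is a cheap improvement worth making before the data are seen.

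**What to change.** 1. **ICU stay and ventilation time (section 4).** Give ICU deaths the worst rank in the Kruskal-Wallis test, or use ICU-free and ventilator-free days to a fixed day with deaths set to 0. Show the survivor-only durations beside it. The worst-rank version uses only what Table 1 already collects. A free-days count must also say how patients discharged before the fixed day are treated afterwards.
2. **ICU-AW.** Keep ICU-AW at discharge as the primary. Add a required sensitivity analysis of being alive without ICU-AW at ICU discharge in all randomised patients, reported with ICU mortality by arm. State how living patients without a discharge score are handled in it.
3. **Section 1.2.** State whether the 10% includes ICU deaths.

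Cost: wording only for the worst-rank version, with no new data and no change in sample size. Death-ranked durations mix mortality with length of stay, which is why the survivor-only figures belong beside them. The sensitivity analysis has less power than the primary: about 84% at 10% mortality and 73% at 20% with all 147 evaluable, and about 80% at 10% mortality with 132.
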